## Abstract

**Background **Disability is prevalent in individuals with multiple sclerosis (MS), leading to difficulty in care access, significant caregiver burden, immense challenges in self-care and great societal burden.  Without highly coordinated, competent and accessible care, individuals living with progressive MS experience psychological distress, poor quality of life, suffer from life-threatening complications, and have frequent but avoidable healthcare utilizations. Unfortunately, current healthcare delivery models present severe limitations in providing easily accessible, patient-centered, coordinated comprehensive care to those with progressive MS. We propose a home-based comprehensive care model (MAHA) to address the unmet needs, challenges, and avoidable complications in individuals with progressive MS with disabling disease.

**Objective **The article aims to describe the study design and methods used to implement and evaluate the proposed intervention.

**Method** The study will use a randomized controlled design to evaluate the feasibility of providing a 24-month, home-based, patient-centered comprehensive care program to improve quality of life, reduce complications and healthcare utilizations overtime (quarterly) for 24 months. A transdisciplinary team led by a MS-Comprehensivist will carry out this project. Fifty MS patients will be randomly assigned to the intervention and usual care program using block randomization procedures. We hypothesize that patients in the intervention group will have fewer complications, higher quality of life, greater satisfaction with care, and reduced healthcare utilization. The proposed project is also expected to be financially sustainable in fee-for-service models but best suited for and gain financial success in valued-based care systems.

**Discussion** This is the first study to examine the feasibility and effectiveness of a home-based comprehensive care management program in MS patients living with progressive disability. If successful, it will have far-reaching implications in research, education and practice in terms of providing high quality but affordable care to population living with severe complex, disabling conditions.

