### Sample size

The sample size estimation is computed based on
**Specific Aim 1**: the increased score of quality of life (QoL) and
**Specific Aim 2**: the reduced number of unplanned healthcare utilizations associated with complications. An estimated 50 patients per group will provide 80% power to detect a 5-point difference [Usual Care mean (SD): 45(8.6), MAHA mean (SD) 50(8.6)] between groups in the SF-36 Mental Health Component Score QoL. This sample size also provides 80% power at a 5% significance level to detect a 34% reduction in unplanned visits/admits (from 2.5 per person per year to 1.65, using the Poisson distribution, which is most appropriate for count/rate data). These are feasible and clinically important differences. Based on our preliminary analyses, 125 patients are currently expected to meet these criteria. Furthermore, based on our previous patient survey results, a high proportion of patients (~80% or n = 100) have expressed a genuine interest in participating in MS research for the benefit of others with this disabling disease. Furthermore, we estimate 50 patients will be a reasonable panel size for the MS-Comprehensivist or care team leader (CTL) in the MAHA model (unpublished report).

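### The abstract randomises fifty patients in all, but the stated 80% power rests on 50 per group (100 in all), and nothing in the article reconciles the two

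*Protocol article*

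**What the plan says.** The protocol article gives the size of the trial in two places.

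- Abstract, Method: "Fifty MS patients will be randomly assigned to the intervention and usual care program using block randomization procedures". No per-group figure is attached, so the plain reading is 50 patients shared between the two programs.
- Methods, Sample size: "An estimated 50 patients per group will provide 80% power to detect a 5-point difference". The planning values follow: "Usual Care mean (SD): 45(8.6), MAHA mean (SD) 50(8.6)] between groups in the SF-36 Mental Health Component Score QoL". The same number is then used for the second planning outcome: "This sample size also provides 80% power at a 5% significance level to detect a 34% reduction in unplanned visits/admits", with rates given as "from 2.5 per person per year to 1.65, using the Poisson distribution".

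Two other statements in the Sample size section bear on which number is meant. The recruitable pool is described as "a high proportion of patients (~80% or n = 100) have expressed a genuine interest in participating in MS research", out of 125 patients expected to qualify. On workload, the article says "we estimate 50 patients will be a reasonable panel size for the MS-Comprehensivist or care team leader (CTL) in the MAHA model".

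The Study design section confirms two groups but gives neither a total nor an allocation ratio.

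**The concern.** Fifty in all and 50 per group cannot both be the randomised number. Both are current statements of the design in the same article, and neither describes superseded text.

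The number randomised and the power are the figures by which readers will judge recruitment and interpret the result. If the trial closes at 50 patients, a reader cannot tell whether it met its target or stopped at half of it. If 50 in all is the true plan, the article attaches an 80% power claim to a trial half the size that the claim needs, and a null quality-of-life result would be read with more confidence than it deserves.

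**Working it through.** **Inputs.** From the Sample size section: means 45 and 50 (difference 5), common SD 8.6, 80% power, 50 per group; rates 2.5 and 1.65 per person-year, Poisson; significance level 5%, which is written in the utilisation sentence and taken here to cover quality of life too. From the abstract: 50 randomised. Assumed, because not stated: 1:1 allocation (implied by the per-group wording) and a two-sided test.

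**Step 1: reproduce the stated power.** Standardised effect = 5/8.6 = 0.581. For *n* per group, the noncentrality parameter is 5 / (8.6 × √(2/*n*)), referred to a noncentral t with 2*n* − 2 degrees of freedom.

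| *n* per group | Noncentrality | Power, two-sided 5% |
|---|---|---|
| 47 | 2.82 | 79.6% |
| 48 | 2.85 | 80.5% |
| 50 | 2.91 | 82.1% |

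So 48 per group are needed, and 50 is that figure rounded up. The normal approximation gives 47 per group. A one-sided 5% test would need only 37 per group (normal approximation), so the two-sided test is the one that fits. The stated calculation is sound for 50 per group.

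**Step 2: quality of life at 50 in all (25 per group).** Noncentrality = 5 / (8.6 × √(2/25)) = 2.06, against a critical value of 2.01. Power is 52.2% by t-test and 53.8% by normal approximation. The difference detectable with 80% power is 6.95, or about 7.0 points. A one-sided 5% test would give 64.9%, still well short of 80%.

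**Step 3: the planned model.** The Data analysis section compares the MSQLI between groups with a linear mixed model over repeated measurements, adjusted for baseline. Table 1 schedules that inventory at baseline, 12 and 24 months. Suppose that the powered score follows this schedule, with equal correlations ρ between visits and a constant treatment effect. The variance of the baseline-adjusted mean of two follow-ups is then SD² × [(1 + ρ)/2 − ρ²]. At 25 per group:

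| Assumed ρ | Variance factor | Power |
|---|---|---|
| 0.4 | 0.54 | 78% |
| 0.5 | 0.50 | 81% |
| 0.6 | 0.44 | 86% |

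The article states no correlation, so this is a range and not a claim about the trial. It shows that the 52% belongs to the unadjusted comparison only.

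**Step 4: utilisation.** On the log rate ratio, with *T* years counted, z = ln(2.5/1.65) / √[1/(*n* × 2.5*T*) + 1/(*n* × 1.65*T*)], and power = Φ(z − 1.96).

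| *n* per group | *T* | z | Power |
|---|---|---|---|
| 50 | 1 year | 2.93 | 83% |
| 25 | 1 year | 2.07 | 54% |
| 25 | 2 years | 2.93 | 83% |

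The stated 80% at 50 per group fits one year of counts. At 25 per group it is lost over one year but kept over 24 months, under a pure Poisson model.

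**Step 5: which number is likelier.** 125 × 0.80 = 100, which matches two groups of 50. A panel of 50 matches a MAHA arm of 50. Together with Step 1, three features of the Sample size section agree with 100 in all. None of them explains the abstract.

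**The case against.** The strongest reply is that this is a dropped phrase in the abstract. The Sample size section is consistent within itself: its power reproduces at 50 per group, and the pool and panel size fit. On that view no calculation is wrong and the trial is adequately sized. Much of this stands. The per-group reading is the likelier one, and the fault is a conflict between two sections. It does not remove the need to correct the text, because the abstract also presents the study as a feasibility evaluation, for which 50 in all would be believable.

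Stronger readings that a reader might infer are not supported:

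- *That the trial has only 52% power.* This holds only if 50 in all is intended, and then only for an unadjusted two-sided comparison of quality of life with equal arms.
- *That baseline adjustment could restore 80% at 25 per group only with a correlation of about 0.7.* That is the answer for a single follow-up. With the two follow-ups of Step 3 averaged, about 0.5 is enough.
- *That all the efficacy aims should become exploratory at 50 in all.* Utilisation counted over 24 months keeps about 83% under a pure Poisson model.
- *That 100 patients leaves no slack, so every interested patient must enrol and only two per group can be lost.* The article describes those currently expected to qualify, not a closed pool. The loss limit rests on an unadjusted test. An allowance for attrition is also something that an article commonly leaves to the full protocol.

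**Conclusion.** The contradiction is real and unreconciled: 50 randomised in the abstract against 100 in the Sample size section. The weight of the article's own figures points to the abstract as the place in error, but does not prove it.

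Its consequence depends on which number is right. With 50 per group, the stated 80% is correct (82% by t-test) and only the abstract is wrong. With 50 in all, the stated quality-of-life power is wrong for the comparison on which it was computed, at about 52% instead of 80%. The power under the planned repeated-measures model cannot then be given without a correlation that the article does not state, and the utilisation power depends on whether one or two years are counted. These figures assume equal allocation, a two-sided 5% level and no loss to follow-up.

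**What to change.** State one randomised total, with its per-group split, in both the abstract and the Sample size section.

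- If the design is 50 per group, change the abstract to 100 patients (50 per group). Nothing else on this point needs to change.
- If 50 in all is intended, change the Sample size section to 25 per group. Restate the quality-of-life power as about 52% for an unadjusted two-group comparison (detectable difference about 7.0 points), or give the power under the planned baseline-adjusted repeated-measures model with its assumed correlation stated. Restate the utilisation power with the follow-up time that it counts: under a pure Poisson model, about 54% over one year or about 83% over 24 months.

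The cost is wording only, with no added patients or visits. On the second branch, the stated quality-of-life power becomes less favourable unless a correlation can be justified.

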## Background

While great strides have been made in the treatment of relapsing forms of multiple sclerosis (MS), many individuals have or will enter a progressive phase of this disease. This phase of disease is dynamic, highly complex and disabling, which presents extensive challenges in all aspects of care delivery
^1,
2^. The progressive phase of MS meets criteria for the description of “a consuming illness” outlined by the Patient-Centered Medical Home Model (PCMH)
^3^. Specific problems and rate of progression vary, but many will have dysfunction in gait
^4,
5^, movement of extremities
^4^, bladder and bowel function
^6,
7^, speech and swallowing
^8^, and respiratory musculature
^9,
10^. Over half will have physical pain
^11^, generally related to neuropathy and/or spasticity
^12^. Cognitive dysfunction
^13^ and depressive mood disorders
^14–
17^ are prevalent. Family members are also likely to suffer from caregiver burden
^18^, mood disorders
^19^ and strain on their own health
^18^. As the disease progresses, a significant proportion of patients will need assistive devices, including power mobility, urinary catheters, gastric tubes, hospital beds, home modifications, and other devices
^1,
2^. Complications can be life threatening, including falls
^20,
21^, urinary tract infections (UTIs)
^22^, respiratory conditions (pneumonia and influenza)
^23,
24^, and pressure ulcers
^21^. Consequently, patients’ health related quality of life decreases substantially as disability ensues
^25^. The MS Society’s White Paper captures the cry of those with progressive MS, who feel “disconnected,” “underserved,” “isolated,” “forgotten,” and “overwhelmed”
^26^. Patients ultimately face the loss of independence in virtually all aspects of life. Still, families desire to keep their loved one at home when possible but acknowledge the overwhelming impact of the disease on the entire family
^27^. Moreover, due to the limitations in mobility, cognition and communication, access to care is highly challenging
^28,
29^. As a result, patients living with progressive phase MS have numerous complex and dynamic healthcare needs that require a range of primary care, specialty, multidisciplinary, and community resources for a long period of time (their life expectancy)
^30,
31^. However, the current care delivery and payment systems contribute barriers and challenges in providing comprehensive coordinated care
^32^, leading to unnecessary healthcare utilization and delayed effective treatments
^33^. Without the comprehensive disease management by a designated provider, the quality of care received is often suboptimal or poor due to the fragmented care system in which the acute care based providers are unfamiliar with patients’ needs, have little knowledge and experience caring for patients with MS
^34^. The combination of the current ambulatory care system utilizes a fee-for-service payment model combined with shortage of MS care specialists leaves no time to address complex chronic care issues or advance care planning
^35–
37^.

To address these problems and gaps in inadequately caring for patients living with progressive MS, we propose a home-based, patient-centered, comprehensive care management program led by a ‘MS-Comprehensivist’. The program is designed to provide a full range of medical and social services for patients and their caregivers, including a transdisciplinary team of primary care providers, specialists, care managers, rehabilitative, social home health, and personal care services. The MS-Comprehensivist who is an advance practice nurse specialized in MS care is responsible to 1) make regular house calls to address patients/family specific needs, 2) coordinate the care with the primary and specialty providers, 3) identify and mobilize other community resources, and 4) provide staff training and patient education in co-managing the complex complications and symptoms. This program, referred to as
**M**ultiple Sclerosis
**A**t
**H**ome
**A**ccess (MAHA), incorporates core principles of the chronic care and patient-centered medical home models. The purpose of the proposed study is to examine the feasibility (e.g., acceptability, utility, implementation, financial sustainability, adaptation and integration)
^38^ and effect of the MAHA model on patient-centered outcomes (i.e., complications, quality of life, satisfaction) and health care utilization outcomes (i.e., unplanned hospitalization and ED visits). The following specific aims were designed to achieve this purpose.

**Specific Aim 1**: To evaluate the effect of the MAHA model on 1) the numbers of complications; 2) patients’ quality of life; and 3) patients’ satisfaction over time (baseline and quarterly).

**Specific Aim 2**: To evaluate the effect of the MAHA model on 1) the numbers of emergency room (ER) visits, and 2) the numbers of unplanned hospitalizations.

**Specific Aim 3**: To evaluate the feasibility of the MAHA model.

1)Acceptability by assessing patient and family experience with the program, as well as provider satisfaction2)Utility by examining the actual use of the program and number of referral received by other providers3)Implementation by evaluating the amount and type of resources needed to implement and factors affecting implementation;4)Adaptation by evaluating the selected elements of the program delivered by tele-health is as effective as face-to-face format.5)Financial sustainability and cost saving by comparing the estimated total cost of the program and financial compensation from payers.

## Conceptual framework

The conceptual framework supporting the MAHA program (
Figure 1) is designed based on the core elements in Wagner’s Chronic Care Model (CCM) and Donabedian’s Structure-Process-Outcome (SPO) model
^39^. First, based on Wagner’s CCM, the MAHA model emphasizes the re-design of existing community and healthcare systems to be patient-centered
^40^. From the patient-provider level, the unique MAHA model again is structured surrounding patients’ needs with the following key components: 1) the productive interaction between informed, activated patient/family and the MAHA team; 2) a transdisciplinary team led by an MS-Comprehensivist who is an advance practice nurse with expertise in MS care, chronic disease management and primary care; 3) care coordination and effective communication among care team members. As a result of re-designing care systems and processes, it is expected that patient outcomes (e.g, complication, quality of life and satisfaction of care) are improved, leading to reduced unplanned healthcare utilizations.

**Figure 1. f1:**
[figure not shown]
MAHA Model Framework adapted from Wagner’s Chronic Care Model.

Besides its function as an acronym for
**M**ultiple Sclerosis
**A**t
**H**ome
**A**ccess, the term
**MAHA** is derived from its city of origin in Omaha, Nebraska, which was settled by Native Americans of the Omaha tribe. In their language, Omaha means “against the wind or current,” which reflects American Indians survival experience from severe weather, disease and scarcity
^41^. While caring for and supporting those MS patients with profound disabling and chronic, complex complications, the caregivers and providers often feel overwhelmed by the environmental barriers, much like the Omaha tribe must have felt centuries ago. Consistent with the core values of these original settlers (earth and sky)
^41^, we honor holistic care which includes evidence-based medicine (earth) and equally holistic care including social, emotional, and spiritual applications (sky).

## Methods

### Study design

The study is a prospective, two-group, randomized experimental design with nine data collection points (baseline and every three months). MS patients recruited from a neurology clinic will be randomized into two groups: the intervention or usual care group. The usual care group receives the current standardized MS care, while the intervention group receives usual care plus 24-months of the MAHA intervention provided by a transdisciplinary team led by a MS-Comprehensivist. The usual care group will receive the intervention at the end of the 24-month period if the intervention is found to be effective by our a priori criteria. The study is subject to review and approval by the University of Nebraska Medical Center Institutional Review Board (IRB) and informed consent will be obtained from all participants prior to the study.

### Study settings

Potential subjects will be identified and recruited from the University of Nebraska Medical Center (UNMC) neurology clinic, where the principle investigator, who has ethical access at the clinic site, will be responsible for identifying the potential participants, screening for eligibility and referring eligible subjects for recruitment.

### Study participants

***Inclusion criteria.*** Patients are eligible for the study if they: 1) have a diagnosis of progressive MS; 2) receive a Kurtzke Expanded Disability Status Scale (EDSS) score ≥6.5 (requires bilateral assist for ambulation and cannot walk > 120 meters;
http://www.nationalmssociety.org/NationalMSSociety/media/MSNationalFiles/Brochures/10-2-3-29-EDSS_Form.pdf); and 3) have a home residence located within 60 miles of the Omaha metropolitan area.

### Sample size

The sample size estimation is computed based on
**Specific Aim 1**: the increased score of quality of life (QoL) and
**Specific Aim 2**: the reduced number of unplanned healthcare utilizations associated with complications. An estimated 50 patients per group will provide 80% power to detect a 5-point difference [Usual Care mean (SD): 45(8.6), MAHA mean (SD) 50(8.6)] between groups in the SF-36 Mental Health Component Score QoL. This sample size also provides 80% power at a 5% significance level to detect a 34% reduction in unplanned visits/admits (from 2.5 per person per year to 1.65, using the Poisson distribution, which is most appropriate for count/rate data). These are feasible and clinically important differences. Based on our preliminary analyses, 125 patients are currently expected to meet these criteria. Furthermore, based on our previous patient survey results, a high proportion of patients (~80% or n = 100) have expressed a genuine interest in participating in MS research for the benefit of others with this disabling disease. Furthermore, we estimate 50 patients will be a reasonable panel size for the MS-Comprehensivist or care team leader (CTL) in the MAHA model (unpublished report).

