### Data analysis

***Specific Aim 1 and 2.*** The data analysis will follow the intention-to-treat (ITT) protocol. To ensure groups are comparable, descriptive analyses, including t-tests and Chi-square tests will be conducted to compare the characteristics of each group at baseline. The occurrence of complications and other self-reported measures, such as ADLs, Multiple Sclerosis QoL Inventory (MSQLI), CSQ-8, and Caregiver Burden Inventory (CBI) will be compared between groups using a linear mixed model to account for the repeated measurements over time and adjust for baseline scores of the respective measures. To determine if differences exist between groups after adjusting for potential confounding variables, such as age, gender, comorbidity, etc. or imbalances between groups, unplanned healthcare utilization (i.e., visits/admissions) will be analyzed using Poisson regression models. The proportion of any versus no use of each health service (e.g., proportion with any inpatient admissions versus the proportion with no admissions) will be compared between groups using Chi-square tests. The time-by-group interaction will be investigated to determine if any changes over time are consistent between groups.

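### Unplanned visits and admissions are sized and tested as Poisson counts with no allowance for patients' rates differing beyond the covariates, and the 80% power figure has no exposure time

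*Protocol article*

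**What the plan says.** The Sample size section of the protocol article states: "This sample size also provides 80% power at a 5% significance level to detect a 34% reduction in unplanned visits/admits". The rates are given as "from 2.5 per person per year to 1.65, using the Poisson distribution, which is most appropriate for count/rate data". The size is set by "An estimated 50 patients per group will provide 80% power" for the quality-of-life score, and the same number is then applied to the count outcome. No period of observation accompanies the annual rates.

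The Data analysis section, under Specific Aim 1 and 2, says that "unplanned healthcare utilization (i.e., visits/admissions) will be analyzed using Poisson regression models", with adjustment for age, gender, comorbidity and the like. It mentions repeated measurements only for the linear mixed model used for the other outcomes. It gives no dispersion parameter, robust variance or patient effect for the Poisson model.

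Under Study design, "the intervention group receives usual care plus 24-months of the MAHA intervention", and data are collected at baseline and then quarterly. The Abstract gives a different size: "Fifty MS patients will be randomly assigned to the intervention and usual care program using block randomization procedures".

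**The concern.** A Poisson model sets the variance of a patient's count equal to its mean, so patients with the same covariates must share one underlying rate. The article gives reason to doubt this. Its Background notes that patients differ in the problems they have and in how fast they progress, and its analysis section expects use to depend on age, gender and comorbidity. Whatever variation the covariates leave makes the Poisson standard error too small. The gap widens as follow-up lengthens, because the variance is understated by the factor 1 + k·mu.

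The stake is a false claim that the programme reduces unplanned use, on one of the two outcomes used to size the trial. The power statement also cannot be interpreted, because an annual rate gives no power until the length of observation is fixed.

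**Working it through.** **Inputs.** From the Sample size section: rates 2.5 and 1.65 per person-year (ratio 0.66, |ln 0.66| = 0.4155), 5% level, 50 per group. From Study design: 24 months. Assumed: two-sided test, equal arms, full follow-up, and k, which the article does not give. k is the squared coefficient of variation of patients' underlying rates, so k = 0.1, 0.25, 0.5 and 1 mean coefficients of about 32%, 50%, 71% and 100%.

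**Step 1: the plan's own figure.** With n per arm and T years,

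power = Φ(0.4155 / √[(1/(2.5T) + 1/(1.65T)) / n] − 1.96).

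| n per arm | T (years) | Standard error | Power |
|---|---|---|---|
| 50 | 1 | √(1.0061/50) = 0.1418 | Φ(0.97) = 83.4% |
| 25 | 2 | √(0.5030/25) = 0.1418 | 83.4% |
| 50 | 2 | √(0.5030/50) = 0.1003 | Φ(2.18) = 98.5% |

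Other standard forms (rate difference, square-root transform, null variance, exact conditional) give 82.5% to 84.4% for the first row. Exactly 80% over one year needs 46 per arm; over two years it needs 23. So the stated figure is met, as a minimum, at about 50 person-years per arm. That is 50 per group for one year or 25 per group for 24 months.

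**Step 2: level of the Poisson test.** With no true effect and 2.5 per year in both arms, mu = 5 over 24 months. The actual level is 2·[1 − Φ(1.96/√(1 + 5k))]. The simulated columns come from 20,000 gamma-Poisson trials per setting, 50 per arm, without covariates.

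| k | 1 + 5k | Level, formula | Level, simulated | Level with robust variance, simulated |
|---|---|---|---|---|
| 0 | 1.0 | 5% | 5.0% | 5.3% |
| 0.1 | 1.5 | 11.0% | 11.0% | 5.4% |
| 0.25 | 2.25 | 19.1% | 19.1% | 5.5% |
| 0.5 | 3.5 | 29.5% | 29.2% | 5.5% |
| 1 | 6.0 | 42.4% | 42.3% | 6.0% |

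The formula does not involve n, so the conflict over sample size does not affect it. On one-year counts (mu = 2.5) it gives 8%, 12%, 19% and 30% at k = 0.1, 0.25, 0.5 and 1.

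**Step 3: power under a valid model, 50 per group, 24 months.** The standard error becomes √[(1/5 + 1/3.3 + 2k)/50].

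| k | Standard error | Power |
|---|---|---|
| 0.1 | √(0.7030/50) = 0.1186 | 94% |
| 0.25 | √(1.0030/50) = 0.1416 | 83% |
| 0.5 | √(1.5030/50) = 0.1734 | 67% |
| 1 | √(2.5030/50) = 0.2237 | 46% |

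The simulated robust test gives 94%, 84%, 68% and 48%. Setting power to 80%: k = [50·(0.4155/2.802)² − 0.5030]/2 ≈ 0.30. The same calculation gives about 0.05 for 50 per group over one year and about 0.02 for 25 per group over 24 months.

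**The case against.** **The planned model has covariates; the check does not.** This stands as a limit on size. Adjustment would absorb an unknown share of the variation, and the entry criteria (progressive disease, EDSS of at least 6.5) may narrow it. The k that matters is what remains, and the article does not show that it is zero.

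**An unseen analysis plan may correct the variance.** It may, and an article need not give every modelling detail. But this article calls Poisson the most appropriate distribution, sizes on it and names Poisson regression. The point concerns that stated choice.

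**A reader might infer that true power is well below 80%.** The documents do not support this. At 50 per group over 24 months, the longer exposure absorbs k up to about 0.30, and no k is given. On the plan's own model, the missing exposure time makes the claim conservative at that size.

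**A reader might infer that 80% fits only one year of follow-up.** It fits 25 per group over 24 months equally well, which is what the Abstract's fifty patients would mean if split equally. The disagreement with 50 per group is a separate point to reconcile.

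**A reader might also infer that the separate outcomes of Aim 2, "1) the numbers of emergency room (ER) visits, and 2) the numbers of unplanned hospitalizations", are underpowered.** That needs a split of the combined rate, which the article does not give. Whether to name one combined outcome is a separate preference.

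**Conclusion.** The concern holds in a conditional form. Any between-patient variation left after covariate adjustment raises the Poisson test above its nominal 5%, whichever sample size or exposure is meant. The figures of 11% to 42% rest on assumed k from 0.1 to 1, a rate of 2.5 per year in both arms, 24-month totals and no covariates. They are a range, not an estimate for this trial.

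On power, what is shown is that the 80% statement lacks an exposure time and a dispersion assumption. A shortfall at 50 per group over 24 months is shown only for k above about 0.30.

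**What to change.** In Data analysis, model each patient's count of unplanned events by negative binomial regression with a log link and the log of time observed as offset, keeping the planned covariates. If quarterly counts are modelled instead, use Poisson regression with robust standard errors clustered on the patient.

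In Sample size, state the exposure time and give power over a range of k, for example 0.1 to 1, once the number per group has been reconciled with the Abstract.

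The cost is wording and a power statement that may be less favourable at larger k; it needs no new data or patients. Holding 80% over 24 months would take about 69 per arm at k = 0.5 and 114 at k = 1, while the Sample size section expects 125 eligible patients and about 100 interested. The proposal is therefore to report the power that the design has, not to enlarge the trial.
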